## Abstract

**Introduction:**

Chronic non-specific low back pain (CNLBP) is a complex condition characterized by pain, dysfunction, disturbed sleep, anxiety, and depression, all of which impair the quality of life. Previous studies showed that practicing Tai Chi had effects on chronic low back pain. However, there is a lack of evidence on its impact on sleep. The trial will evaluate the use of Tai Chi as a treatment for insomnia in elderly people with CNLBP.

**Methods:**

The study design will be a randomized, controlled, open-label trial. Participants (*n* = 106) will be recruited from the Hospital of Chengdu University of Traditional Chinese Medicine, Qing Yang District University for the Elderly, and Ci Tang Street Community. Participants will be randomly assigned to the Tai Chi group (*n* = 53) and the control group (*n* = 53). The Tai Chi group will undergo a Yang-style 24-form Tai Chi program for 8 weeks. The control group will have a waiting period of 8 weeks, followed by 8 weeks of Tai Chi practice. The primary outcomes of this study will be changes in sleep quality and pain intensity. Secondary outcomes of interest will include changes in the quality of pain, range of motion, physical performance, social support, and overall quality of life. Any adverse events and attendance rates will also be reported in this study.

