## Methods

### Study design

This study design conducts an open-label, randomized, controlled trial. The study protocol was approved by the Ethics Committee of the Hospital of Chengdu University of Traditional Chinese Medicine in Sichuan Province on 06/06/2022 (ethics approval number: 2022KL-038-02). This trial is registered with the Chinese Trial Registry under the number ChiCTR2200064977. This protocol adheres to the Consolidated Standard of Reporting Trials (CONSORT) and the Standard Protocol Items: Recommendations for Interventional Trials (SPIRIT). This study will be conducted at the Hospital of Chengdu University of Traditional Chinese Medicine, Qing Yang District University for the elderly, and Ci Tang Street Community. We will compare the effects of the Tai Chi group against the control group on insomnia in elderly people with CNLBP. Baseline assessments and follow-up assessments will be conducted at weeks 8, 16, 32, and 40 to measure primary outcomes such as sleep and pain intensity as well as secondary outcomes such as quality of pain, range of motion, physical performance, social support, quality of life, attendance rate, and adverse events. The detailed schedule of patient interventions and outcomes is described in Table 1.

**Table 1 T1:** Schedule of patients, intervention, outcomes.

**Item**	**Week 0**	**Week 1–8**	**Week 8**	**Week 9–16**	**Week 16**	**Week 32**	**Week 40**

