### Participants

#### Sample size

This study will be designed to compare the effectiveness of the Tai Chi group against the control group. Sample size calculations will be based on the change in the Pittsburgh Sleep Quality Index (PSQI) and the Visual Analog Scale (VAS) scores. The study will detect a 5-point difference between groups on the PSQI scores (Irwin et al., 2008) and a 1.96-point difference in the VAS scores (Bower and Irwin, 2016). A total sample size of 96 participants will achieve 90% power with an alpha of 0.05. However, considering a 10% drop rate, we plan to recruit 106 patients.

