### Outcome measurements

#### Primary outcomes

##### Sleep

The primary outcome is the PSQI (Pittsburgh Sleep Quality Index) scores, which are the most commonly used measure of sleep quality and consist of 19 questions about sleep habits over a 1-month period (Nadal-Nicolas et al., 2020). The PSQI measures sleep quality, sleep latency, sleep duration, habitual efficiency, disturbances, use of sleeping medications, and daytime dysfunction (Pachikian et al., 2021). The scores range from 0 to 21, with higher scores indicating worse sleep quality. A score >5 indicates clinical sleep impairment (Kalmbach et al., 2020).

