### Statistical analysis

The statisticians and researchers will establish a statistical plan. It will contain baseline characteristics, treatment effects, adverse events, and attendance evaluations. All analyses will be conducted using the intention-to-treat method. Two independent sample t-tests will be used for analysis. Repeated measures analysis of variance will be used to examine the effects of VAS between the Tai Chi group and the control group. We will use the Wilcoxon-Signed Rank Test to assess non-normally distributed data. Continuous data will be expressed as mean ± standard deviation. The chi-square test will be used for categorical data. We will set the statistical significance at a *P*-value of < 0.05. Missing data will be processed according to the last observation carry-forward rules. We will use IBM SPSS Statistics version 25 (SPSS, Inc., USA) for data analysis.

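### PSQI and VAS are both primary at an undivided 0.05 with no rule on whether either or both must succeed, so the error rate of a primary claim and the meaning of the 90% power are left open

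*Protocol article*

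**What the plan says.** The protocol article describes the primary outcome in several places.

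- Abstract, Methods: "The primary outcomes of this study will be changes in sleep quality and pain intensity".
- Study design: the visits serve "to measure primary outcomes such as sleep and pain intensity". This again gives two outcomes, worded as examples.
- Outcome measurements: PSQI (under Sleep) and VAS (under Pain intensity) stand side by side beneath a plural heading for primary outcomes. The Sleep text nevertheless opens in the singular: "The primary outcome is the PSQI (Pittsburgh Sleep Quality Index) scores".
- Sample size: differences are given for both scales, 5 points on PSQI and 1.96 points on VAS. They are followed by one joint statement: "A total sample size of 96 participants will achieve 90% power with an alpha of 0.05".
- Statistical analysis: "We will set the statistical significance at a *P*-value of < 0.05". No division of alpha, testing order or requirement that both outcomes succeed is given.

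The Introduction hypothesises benefit on insomnia, pain and functioning together, also without a decision rule.

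**The concern.** With two primary outcomes, the meaning of a positive trial depends on a rule that the article does not give. If a significant result on either scale is enough, testing each at 0.05 gives an overall false-positive chance above 0.05. If both must be significant, the error rate is safe, but the chance of success is below the power of the weaker test unless the 90% was worked out for the pair.

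The gap matters in practice. The stated question is insomnia, while the Introduction treats a benefit of Tai Chi on low back pain as already supported. As the text stands, a significant VAS with a null PSQI could be reported as a positive primary result and leave the new question unanswered. Participants are not blinded and both scales are self-reported, so the rule is best fixed before the data are seen.

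**Working it through.** **Inputs from the article.** Two primary outcomes (Abstract; Study design; Sample size). Significance level 0.05 (Sample size; Statistical analysis). Power 90%, total N = 96, 1:1 allocation, hence 48 per arm. Differences of 5 (PSQI) and 1.96 (VAS).

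**Assumptions.** Two-sided tests, as sidedness is not stated. Normal approximation. The correlation between the two test statistics is not given, so a range is shown.

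**1. The plan's own figure.** N = 96 cannot be reproduced because no standard deviations are given. It can only be inverted: SD = difference × √(48/2) / (1.960 + 1.2816).

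- PSQI: 5 × 4.899 / 3.2415 = 7.56.
- VAS: 1.96 × 4.899 / 3.2415 = 2.96.

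These are the SDs at which each outcome, taken alone, has 90% power with 48 per arm. Nothing in the article says that either was used.

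**2. Either outcome suffices.** With independent tests, the false-positive chance is 1 − 0.95² = 0.0975. With correlation ρ, it is 1 − P(|Z₁| < 1.96 and |Z₂| < 1.96) under a bivariate normal:

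| ρ (assumed) | False-positive chance |
|---|---|
| 0 | 9.75% |
| 0.3 | 9.5% |
| 0.5 | 9.1% |
| 0.7 | 8.3% |
| 0.9 | 7.0% |

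The ratio to the nominal 5% is 1.95 at ρ = 0 and about 1.4 at ρ = 0.9. The Introduction describes sleep and pain as linked, so the true value is probably below 9.75%.

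**3. Both must succeed.** Type I error is at most 0.05. Joint power is P(Z₁ < a and Z₂ < b), where a and b are the normal quantiles of the two individual powers.

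| ρ (assumed) | 90% and 90% | 90% and 99% |
|---|---|---|
| 0 | 81.0% | 89.1% |
| 0.3 | 82.2% | 89.3% |
| 0.5 | 83.2% | 89.5% |
| 0.7 | 84.7% | 89.8% |

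The first power column applies only if both outcomes sit at exactly 90%. Two outcomes with different target differences would rarely need the same N. If 96 is the larger of two requirements, the other outcome has more than 90% power and the second column is nearer.

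**4. PSQI alone is primary.** There is one test at 0.05, so there is no inflation and no joint power to compute.

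**5. Why a later alpha split is not free.** If alpha were divided equally (0.025 each), the error rate would be at most 1 − 0.975² = 4.94%. An outcome with exactly 90% power at 0.05 would then have Φ(3.2415 − 2.2414) = 84.1% power with 48 per arm.

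**The case against.** The strongest reply is that the article specifies no inflated procedure. It never says that success on either scale is enough. If both are required, or if the Sleep sentence is taken literally, the error rate stays at 0.05. That stands, and the inflation can only be stated conditionally.

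A reader might infer that the stated alpha and power cannot both hold under any rule. The documents do not support this. With PSQI alone as primary, nothing here contradicts either figure. With both required, the 90% could be the joint figure, or the joint power could be close to 90%.

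A reader might also count both outcomes at all four follow-up visits as separate primary tests and arrive at a much larger error rate. The documents do not support that either. Those measurements are repeated on the same people and are not independent. No section makes each visit a primary test, and Statistical analysis gives VAS a repeated measures analysis of variance.

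The singular wording under Sleep is a minor conflict. The plural heading and the parallel Pain intensity section make two primary outcomes the natural reading.

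Finally, Statistical analysis says that a statistical plan will be established, and a multiplicity rule could sit there. This lowers confidence that error control is absent, but it does not settle the point. The article itself fixes the number of primary outcomes, an undivided alpha and an unattributed power, and the sample size depends on the rule. A later alpha split would weaken the power statement, as step 5 shows.

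**Conclusion.** The point holds in conditional form. The article sets two primary outcomes at an undivided 0.05 and does not say what counts as success.

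- If either outcome is enough, the chance of a false-positive primary claim is up to 9.75%, falling to 7.0% at a correlation of 0.9.
- If both must succeed, or PSQI alone is primary, type I error is not inflated.
- The 90% power cannot be attached to an outcome or a combination. Joint power of 81–85% is one assumed case (exactly 90% on each outcome, correlation 0 to 0.7), and values close to 90% are equally compatible with the text.

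The figures rest on two-sided tests, a normal approximation and assumed correlations. They do not establish that the trial as planned has an error rate near 10%, only that the text permits a reading under which it would. The remedy is a cheap improvement rather than the repair of a fatal fault.

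**What to change.** State a fixed sequence. PSQI at week 8 is the first primary test at two-sided 0.05. VAS at week 8 is tested at two-sided 0.05 only if PSQI is significant. Other visits and outcomes are reported with confidence intervals and without confirmatory claims. Week 8 is the last visit before the control group starts Tai Chi, so it is the clean randomised comparison. The sequence holds the overall error at 0.05 and keeps full alpha for the insomnia question.

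Align the Abstract, Study design, Sample size, Sleep and Pain intensity sections with this, and say which outcome the 90% power refers to. Statistical analysis should name the week 8 VAS comparison used in the sequence, since it now gives only a repeated measures analysis for VAS.

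Cost: the PSQI test needs no added participants. There is no confirmatory VAS claim if PSQI fails, so the chance of such a claim equals the joint power in step 3. The primary-endpoint wording must be amended in the protocol and the registration. Requiring both outcomes or splitting alpha would also be valid, with the power consequences shown in steps 3 and 5.

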**Clinical trial registration:**

ChiCTR2200064977.

## Introduction

Low back pain is a public health problem that primarily affects women between the ages of 40 and 80 worldwide (Hill et al., 2011; Hoy et al., 2012; Knezevic et al., 2021). The prevalence of low back pain is 84%, and the disability rate is 11–12% (Albazli et al., 2021). Low back pain is a significant source of social and economic burden (Comachio et al., 2015). The disease's global burden is expected to rise due to an increase in the aging population and population growth (DALYs and Collaborators, 2016). Low back pain presents in two forms: non-specific or mechanical (Will et al., 2018). Chronic non-specific low back pain (CNLBP) is defined as persistent pain that lasts for more than 12 weeks and that occurs in the lower part of the spine between the dorso-lumbar and the lumbosacral hinges. It is not associated with specific pathologies, such as infections, tumors, osteoporosis, or lumbar spine fractures (Balague et al., 2012; Mu et al., 2020; Kabore et al., 2022). CNLBP affects up to 90% of patients, with a prevalence of 2–7% among those who suffer from chronic pain (Bellido-Fernandez et al., 2022). CNLBP is the result of a complex interplay between physical factors (such as disability, muscular strength and endurance, and body composition), psychological factors (such as pain self-efficacy, depression, anxiety, and sleep quality), and social factors (such as social functioning and support networks) (Iglesias-Gonzalez et al., 2013; Rodrigues-De-Souza et al., 2016; Lall and Restrepo, 2017; Volpato et al., 2019; Tagliaferri et al., 2020; Ho et al., 2022). It is the greatest cause of disability and is associated with age, sleep quality, BMI, smoking habits, and co-morbidity (Sidiq et al., 2021). Insomnia and disrupted sleep negatively affect pain, functional ability, anxiety, depression, and the quality of life of patients with CLBP (Akodu and Akindutire, 2018; van de Water et al., 2011). According to a study by Marin et al. (2006), individuals with CNLBP experienced a 55% decrease in sleep quality when their pain increased. Evidence indicates that participants with CLBP are at 2.4 times greater risk of experiencing sleep problems (Stubbs et al., 2016). Poor sleep quality in participants with CLBP is moderately correlated with physical disability (McCracken and Iverson, 2002). Therefore, improving sleep quality may be beneficial for patients with CNLBP. A study by Bedaiwi et al. (2016) showed that, while celecoxib had a protective effect on patients with CNLBP, this treatment did not result in any changes in the inflammatory lesions of the sacroiliac joints or the spine. A prospective study has indicated that non-steroidal anti-inflammatory drugs (NSAIDs) have therapeutic effects on patients with CNLBP (Takahashi et al., 2017). However, 3–23% of patients discontinue NSAID therapies owing to their side effects (Schnitzer et al., 2004). Chung et al. (2013) found that opioids and partial opioid agonist drugs provide pain relief in patients with CNLBP. Several studies have reported the use of opioids to treat CNLBP. However, they are often accompanied by insomnia (Benca et al., 1992; Benca, 1996; Latif et al., 2019). Evidently, pharmacotherapy alone is insufficient to effectively treat insomnia in patients with CNLBP. Clinical guidelines indicate that self-management, exercise therapy, and cognitive behavioral therapy have been shown to have positive effects on CLBP (Savigny et al., 2009; Koes et al., 2010; Eadie et al., 2013). A recent randomized controlled trial found that moderate-intensity exercise training has a positive effect on sleep quality (Tseng et al., 2020). However, research examining the effectiveness of exercise therapy in improving insomnia in patients with CNLBP is scarce.

Tai Chi, developed a few hundred years ago, is a traditional Chinese mind-body practice that combines physical, psychosocial, and social factors to promote health. It is an ancient discipline characterized by flowing circular movements of the upper limbs and constant weight shifting in the lower limbs (Peng, 2012; Dong et al., 2022; Song et al., 2022). Tai Chi has five forms: Chen, Yang, Wu, Sun, and Wu/Hao. Tai Chi is an exercise of mild-to-moderate intensity for older people (Siu et al., 2021a). Several studies have investigated the effects of Tai Chi on Parkinson's disease, diabetes, anxiety, depression, and so on Yeh et al. (2009); Li et al. (2012); Liu et al. (2020). Recent studies report Tai Chi to be a viable alternative for managing insomnia (Siu et al., 2021b). Tai Chi has been shown to have beneficial effects on insomnia in breast cancer survivors (Irwin et al., 2017). The study concluded that Tai Chi can effectively improve pain and disability in people with persistent low back pain (Hall et al., 2011; Liu et al., 2019). Tai Chi also has protective effects on the neuromuscular function of the lower extremities in aging patients with CNLBP (Zou et al., 2019). Tai Chi may be a potential alternative method to affect cognitive appraisal outcomes (Hall et al., 2016). However, it is unknown whether Tai Chi is an effective treatment for insomnia in patients with CNLBP.

We will conduct a randomized controlled trial to evaluate Tai Chi's effectiveness in managing insomnia in elderly people with CNLBP. We hypothesize that Tai Chi will be more effective in improving insomnia, pain, and physical and social functioning than the control group.

## Methods

### Study design

This study design conducts an open-label, randomized, controlled trial. The study protocol was approved by the Ethics Committee of the Hospital of Chengdu University of Traditional Chinese Medicine in Sichuan Province on 06/06/2022 (ethics approval number: 2022KL-038-02). This trial is registered with the Chinese Trial Registry under the number ChiCTR2200064977. This protocol adheres to the Consolidated Standard of Reporting Trials (CONSORT) and the Standard Protocol Items: Recommendations for Interventional Trials (SPIRIT). This study will be conducted at the Hospital of Chengdu University of Traditional Chinese Medicine, Qing Yang District University for the elderly, and Ci Tang Street Community. We will compare the effects of the Tai Chi group against the control group on insomnia in elderly people with CNLBP. Baseline assessments and follow-up assessments will be conducted at weeks 8, 16, 32, and 40 to measure primary outcomes such as sleep and pain intensity as well as secondary outcomes such as quality of pain, range of motion, physical performance, social support, quality of life, attendance rate, and adverse events. The detailed schedule of patient interventions and outcomes is described in Table 1.

**Table 1 T1:** Schedule of patients, intervention, outcomes.

**Item**	**Week 0**	**Week 1–8**	**Week 8**	**Week 9–16**	**Week 16**	**Week 32**	**Week 40**
**Patients**							
Informed consent	×						
Inclusion criteria	×						
Exclusion criteria	×						
**Intervention**							
Tai Chi group		×					
Control group		×		×			
**Outcomes**							
PSQI	×		×		×	×	×
VAS	×	×	×	×	×	×	×
Quality of pain	×		×		×	×	×
Range of motion	×		×		×	×	×
JOA	×		×		×	×	×
ODI	×		×		×	×	×
CPSS	×		×		×	×	×
SSRS	×		×		×	×	×
SF-36	×		×		×	×	×
Adverse events			×		×	×	×
Attendance rate			×		×	×	×

PSQI, Pittsburgh Sleep Quality Index; VAS, Visual Analog Score; JOA, Japanese Orthopedic Association Scores; ODI, Oswestry Disability Index; CPSS, Chronic Pain Self-Efficacy Scale; SF-36, Short Form 36; SSRS, Social Support Rating Scale.

### Participants

#### Sample size

This study will be designed to compare the effectiveness of the Tai Chi group against the control group. Sample size calculations will be based on the change in the Pittsburgh Sleep Quality Index (PSQI) and the Visual Analog Scale (VAS) scores. The study will detect a 5-point difference between groups on the PSQI scores (Irwin et al., 2008) and a 1.96-point difference in the VAS scores (Bower and Irwin, 2016). A total sample size of 96 participants will achieve 90% power with an alpha of 0.05. However, considering a 10% drop rate, we plan to recruit 106 patients.

#### Inclusion criteria

To be included in the study, the participants must meet the following criteria:

(a) be between 60 and 75 years of age;(b) diagnosed as having CNLBP as defined by the American College of Physicians and the American Pain Society. CNLBP is characterized by pain in the waist and the lumbosacral region, mainly located below the rib margin of the back and above the hip fissure, and may be accompanied by thigh pain, lumbar weakness, lumbar stiffness, limited lumbar mobility, with no nerve root compression, spinal canal stenosis, and trauma (Chou et al., 2007; Chen et al., 2022).(c) suffering from CNLBP for more than 3 months;(d) having no infectious inflammation, fractures, or tumors in the lower back; and(e) willing to sign informed consent.

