#### Exclusion criteria

Participants will be excluded from the study if they:
(a) have severe joint pain or deformity or severe spinal deformity;(b) have serious diseases that affect mobility, such as myocardial infarction or stroke, congestive heart failure, severe chronic obstructive pulmonary disease, cancer, and other serious diseases; and(c) have had any Tai Chi training or have participated in other clinical trials.

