## Discussion

This study will compare the effectiveness of Tai Chi in improving insomnia symptoms in elderly people with CNLBP in the Tai Chi group with that in the control group. Previous research showed that Tai Chi provides various benefits for older adults with CLBP, including improvements in functional abilities (such as balance, leg strength, and flexibility), psycho-spiritual support, and social support (Lee et al., 2020). That study was conducted with 18 participants, who were randomized into the Tai Chi group. In our study, 122 participants will be recruited. Previous studies suggest that Tai Chi has protective effects on neuromuscular function in aging individuals with non-specific low back pain, but no follow-up was reported (Zou et al., 2019; Liu et al., 2020). Our study will fill this gap by conducting a 24-week follow-up to evaluate the effects of Tai Chi on insomnia in people with CNLBP. Previous studies mostly focused on the functional benefits of Tai Chi (Wen et al., 2022; Yan et al., 2022). However, this study will aim to test the effectiveness of Tai Chi in treating insomnia in patients with CNLBP.

This trial will have several strengths that increase its validity and reliability. First, the randomized controlled trial design of the study allows for a fair comparison of the effects of Tai Chi on insomnia in patients with CNLBP. Second, the study takes into account multiple factors that affect sleep quality, such as physical, psychological, and social factors. Additionally, the protocol adheres to CONSORT and SPIRIT guidelines.

However, this study will also face some limitations. First, the high expectations of the participants in the Tai Chi group may influence the results. Second, there is a risk of high dropout rates during the waiting period. Finally, the research process may be affected by COVID-19.

The results of this trial may help improve sleep quality and reduce pain in people with CNLBP. Furthermore, they could advocate for the promotion of Tai Chi training as a therapeutic option to treat insomnia in elderly individuals with CNLBP. Tai Chi may be considered a viable therapeutic option for CNLBP patients with insomnia.

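### The trial sets out to treat insomnia, but no eligibility criterion requires poor sleep, so people without sleep impairment can be enrolled and a positive result would not support a conclusion about insomnia

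*Protocol article*

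**What the plan says.** The Abstract (Introduction) gives the aim: "The trial will evaluate the use of Tai Chi as a treatment for insomnia in elderly people with CNLBP". The main Introduction repeats it as objective and hypothesis. The Discussion ends on the same claim: "Tai Chi may be considered a viable therapeutic option for CNLBP patients with insomnia".

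The Inclusion criteria section begins "To be included in the study, the participants must meet the following criteria" and lists five items:
- (a) "be between 60 and 75 years of age"
- (b) a CNLBP diagnosis
- (c) "suffering from CNLBP for more than 3 months"
- (d) no infection, fracture or tumour in the lower back
- (e) willingness to consent

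The Exclusion criteria cover joint and spinal problems ("have severe joint pain or deformity or severe spinal deformity"), serious disease affecting mobility, and previous Tai Chi training or participation in other trials. Sleep appears in neither list. Under Recruitment, the posters show these same inclusion criteria and the lectures are about Tai Chi, so recruitment does not select for poor sleep either.

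Under Primary outcomes (Sleep), the PSQI runs from 0 to 21, higher being worse, and the protocol gives a threshold: "A score >5 indicates clinical sleep impairment". Table 1 schedules the PSQI at week 0. The Sample size section states: "The study will detect a 5-point difference between groups on the PSQI scores".

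**The concern.** The condition named in the aim and the conclusion is not a condition of entry. If the lists are followed as written, someone who sleeps well is eligible. Two things are at stake.

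- **Interpretation.** A treatment effect averaged over people with and without sleep impairment does not show that insomnia was treated, and the Statistical analysis section names no analysis that isolates the impaired participants.
- **Consistency with the design effect.** The trial is sized on a 5-point PSQI difference, and people entering at the low end of the scale have little or no room to improve by that much.

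**Working it through.** **Step 1: aim against eligibility.** The aim, hypothesis and closing claim all name insomnia. The five inclusion items and three exclusion items contain nothing on sleep. The lists are lettered and presented as what participants must meet, so the gap cannot be put down to the article condensing a longer protocol. Eligibility is also not something that a statistical analysis plan would supply.

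**Step 2: room on the scale.** By the protocol's cut-off, an unimpaired sleeper has a baseline PSQI of 0 to 5. The floor is 0, so the largest possible fall equals the baseline score:
- baseline 0 to 4: at most 4 points, so a 5-point fall is impossible;
- baseline 5: exactly 5 points, and only by reaching 0.

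**Step 3: the stated sample size.** The inputs are 96 evaluable participants (48 per arm at 1:1), 90% power, alpha 0.05 (two-sided assumed) and a 5-point difference. No SD is stated, so 96 cannot be reproduced. Solving backwards with the two-sample t-test gives a standardised effect of 0.669, hence SD = 5 / 0.669 = about 7.48. The normal approximation gives (1.960 + 1.282) / √24 = 0.662 and SD about 7.56. This back-solved SD holds only if the PSQI alone determined N. The Sample size section also names a 1.96-point VAS difference, and if that set N, nothing follows about the PSQI SD.

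**Step 4: what dilution could do.** Assumptions, none taken from the document: a 5-point effect in those with PSQI >5, a 1-point effect in those with PSQI ≤5, and p the share of the latter. Mean effect = 5(1 − p) + 1·p. Power is from the non-central t distribution with 48 per arm, two-sided 0.05.

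| Share p | Mean effect | Power, SD 7.48 | Power, SD 4.5 |
|---|---|---|---|
| 20% | 4.2 | 78% | 99% |
| 30% | 3.8 | 69% | 98% |
| 40% | 3.4 | 60% | 96% |
| 50% | 3.0 | 49% | 90% (0.898) |

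The mean effect falls in every row. Whether power suffers depends almost entirely on the SD.

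**Step 5: restricting the analysis to baseline PSQI >5.** With the full 5-point effect, SD 7.48 and 48(1 − p) per arm, power is 82%, 77%, 70% and 62% at p = 20%, 30%, 40% and 50%. At this SD that is better than the diluted comparison but does not restore 90%.

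**The case against.** A fair defence has five parts.

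1. **Good sleepers may be few.** The Introduction cites a 2.4-fold risk of sleep problems in chronic low back pain. A raised risk does not mean that every patient is affected, and no section gives the share. A reader might infer that good sleepers will enter in numbers, but the document supports only that they can.

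2. **The 5 points are a between-group mean difference.** They are not a fall required of each participant. Controls may worsen, and poor sleepers may improve by more than 5. A reader might infer that the trial cannot reach its 5-point difference. That does not follow: the floor limits individuals at 0 to 5 and does not make the group contrast unattainable. The 5 points are also a planning value, so a smaller observed difference is not in itself a failed trial.

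3. **A power shortfall is not shown.** An SD near 7.5 is large for a 0 to 21 scale. An even spread over all 22 scores has SD √((22² − 1)/12) = 6.3, although the SD of change scores could differ. At SD 4.5, power stays close to or above 90% throughout. A reader might infer that the trial is underpowered for this reason, but with neither the SD nor the share stated, that is unproven.

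4. **The randomised comparison stays valid for the outcome as named.** The Abstract gives the primary outcomes as sleep quality and pain intensity, the Discussion also speaks of sleep quality in CNLBP, and its insomnia sentence is hedged. This stands, and it is why rewording is an adequate remedy. It does not rescue the stated aim, which names insomnia.

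5. **PSQI >5 is not an insomnia diagnosis.** Correct: the protocol calls it clinical sleep impairment. The cut-off narrows the gap but does not by itself justify the word insomnia.

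A reader might also extend the point to pain, since no minimum VAS is set. Entry already requires a diagnosed pain condition of more than 3 months, so the same mismatch does not arise there.

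**Conclusion.** The point holds as a mismatch between the enrolled population and the claim. Followed exactly, the protocol can enrol people without sleep impairment by its own threshold, and a positive result would then describe sleep quality in CNLBP patients not selected for poor sleep, rather than treatment of insomnia. This part rests on the text alone and needs no assumption about SD or numbers.

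The effect on the PSQI comparison is directional only. Entrants at 0 to 5 would tend to pull the mean difference below the 5 points used for sizing. The loss of power is unknown: in the assumed 30% scenario it ranges from substantial (69% at SD 7.5) to negligible (98% at SD 4.5). These figures illustrate and should not be quoted as the trial's power. The pain outcome is not affected.

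**What to change.** **Preferred, if enrolment has not begun:** add to the Inclusion criteria a PSQI above 5 at the week-0 assessment, which is the protocol's own cut-off on an instrument already scheduled then. Describe the resulting population as having clinical sleep impairment, unless an insomnia diagnosis is also required. The cost is a protocol amendment, some screen failures and slower recruitment. Room to improve stays limited just above the cut-off (a participant at 6 must reach 1 to fall by 5), so the 5-point difference should be justified for that population.

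**If the broader population is kept, or enrolment has begun:** restate the objective and conclusion as sleep quality in elderly people with CNLBP. Keep the intention-to-treat comparison of all randomised participants as primary, in line with the Statistical analysis section. Prespecify the baseline PSQI >5 subgroup as a supporting analysis and state its reduced precision. Making that subgroup the primary population instead would conflict with the intention-to-treat commitment unless that section were revised, and would cost sample size (the 82% to 62% power in the last step of the working, at SD 7.48). The cost of this route is rewording and one additional prespecified analysis.
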